**Follow-up**

The follow-up for efficacy outcomes will conclude at hospital discharge. Safety outcomes will be reported until 30 days after hospital discharge.

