**Outcomes**

**Primary Outcomes:**

Composite outcome of mechanical ventilation and/or hospitalization longer than 14 days and/or in hospital-death

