**Secondary Outcomes:**

- Clinical: days of oxygen requirement; days in mechanical ventilation; days of high-flow nasal cannula (HFNC) requirement; multiple organ dysfunction score (SOFA) (day 0, 3 and 7); days in intensive or intermediate care unit (ICU); time to respiratory failure development (Pa0_2_/FiO_2_<200 or, if arterial blood gases are not available on that day, a sustained Sa02/Fi02< 214 will be considered equivalent); length of hospitalization; 30 day-mortality.
- Microbiological: SARS-Cov2 PCR clearance in nasopharyngeal swab (days 0, 3 and 7)
- Inflammatory markers kinetics: lymphocyte count, C-reactive protein, procalcitonin, lactate dehydrogenase (LDH), D-dimer, ferritin and IL-6 evolution on days 0, 3, and 7.
- Radiologic: chest CT scan pneumonia score or portable chest X-ray progression between days 0 and 5.

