**Data collection and management**

Study follow-up and the variables that will be collected are described below.

Baseline:

Demographics, comorbidities, medications, sequential organ failure assessment (SOFA) score [31], days of COVID-19 since symptoms initiation, characteristics of COVID-19 symptoms at debut and at hospitalization, date of hospitalization.

Hemodynamics: heart rate, systolic and diastolic blood pressure, temperature, peripheral arterial 02 saturation, respiratory rate, arterial blood gases.

Evolution:

SOFA criteria daily until day 30 or discharge

Temperature daily until day 30 or discharge

Hemodynamics daily until day 30 or discharge

Respiratory function daily until day 30 or discharge: oxygen requirements, type of support, daily SaO2/FiO2, PaO2/FiO2 on day 0, 3, 7, 14 and 21.

Register of vasoactive drugs until day 30 or discharge

Register of antibiotics, antivirals until day 30 or discharge

Register of steroids and other immunomodulators until day 30 or discharge

Register of anticoagulants and thromboprophylaxis until day 30 or discharge

All-cause mortality at hospital discharge, and at 30 days

Cause of death.

Laboratory:

Total lymphocyte count; C-reactive protein, procalcitonin, LDH, D-dimer, troponin, pro-BNP, ferritin and IL6 evolution on days 0, 3 and 7.

SARS-Cov2 PCR in nasopharyngeal swab and in plasma on days 0, 3 and 7.

IgG SARS-CoV-2 titers on days 0, 3 and 7.

SARS-CoV-2 neutralizing antibodies capacity on day 0.

Imaging:

High-resolution chest CT scan at enrolment (day 0), and at day 5. If the patient has a contraindication or is unable to undergo a CT scan, a portable chest X-ray will replace it. For CT analysis and interpretation we will use three previously validated imaging scores for COVID pneumonia severity^6–9^. For the radiologic analysis when a chest CT scan cannot be performed and is replaced by a portable chest X-ray, we will add a blinded thoracic radiologist expert evaluation for improvement, stability or worsening of lung infiltrates.

Quality control:

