**Statistical Analysis Plan**

Continuous variables will be shown as mean and standard deviation for normally data or median and interquartile range elsewhere. Categorical variables will be shown as the number of cases and percentages

Primary outcome

We will assess the effect of early plasma compared to delayed plasma on the primary binary outcomes through chi-squared tests or Fisher’s exact test when appropriate, and odds ratios will be presented together with 95% CI and p-values. In addition, as an exploratory analysis we will adjust for age and SOFA score at enrolment, and clinically significant baseline variables if they result imbalanced between both study arms, as fixed (individual-level) effects, using logistic regression. Values of p<0.05 (2 tails) will be considered.

Secondary outcomes

We will assess the effect of early plasma compared to delayed plasma on the secondary binary variables through chi-squared tests or Fisher’s exact test when appropriate. For continuous variables with normal distribution we will use the t-test, and for continuous variables with non-normal distribution the Wilcoxon-rank-sum test or Mann-Whitney U test for comparisons. Additionally, we will analyze binary variables using logistic regression. Numerical variables will be examined using generalized linear models with log link function and gamma family function. Treatment effects, crude and adjusted, will be presented as exponentiated coefficients, i.e. odds ratios, hazard ratios or incidence rate ratios, respectively and treatment effect estimates will be presented with 95% CI.

To test difference between Kaplan-Meier estimates in survival analysis, we will use the Log-Rank test and/or Cox proportional hazard models for time-to event variables.

For the analysis of paired continuous variables, we will use Wilcoxon matched-pairs signed-rank test.

Statistical significance will be defined using a 2-sided significance level of α = .05.

Immune response subgroup analysis

A pre-planned analysis of baseline neutralizing antibodies titers and anti-SARS-CoV-2 IgG titers progression (on days 0, 3, 7), is planned for participants from the early plasma group and for the subset of participants from the deferred plasma group who will not have yet received plasma on those scheduled days. Groups will be compared through Chi-squared tests or Fisher’s exact test when appropriate.

Statistical significance will be defined using a 2-sided significance level of α = .05.

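### Ending efficacy follow-up at discharge conflicts with the 30-day mortality outcome, makes discharge an informative censoring point for time to respiratory failure, and leaves events after an early discharge outside the primary composite

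*Combined protocol and SAP*

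**What the plan says.** All references are to the combined protocol and SAP.

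- **Follow-up:** "The follow-up for efficacy outcomes will conclude at hospital discharge". The next sentence reads: "Safety outcomes will be reported until 30 days after hospital discharge".
- **Secondary Outcomes:** the clinical list ends with "length of hospitalization; 30 day-mortality" and also contains time to respiratory failure, defined by a PaO2/FiO2 threshold or its saturation equivalent.
- **Data collection and management:** "All-cause mortality at hospital discharge, and at 30 days", with cause of death. The daily clinical lines are bounded differently, for example "Respiratory function daily until day 30 or discharge".
- **Primary Outcomes:** "Composite outcome of mechanical ventilation and/or hospitalization longer than 14 days and/or in hospital-death". The section gives no rule for readmission and no origin for the 14 days.
- **Statistical Analysis Plan, secondary outcomes:** "To test difference between Kaplan-Meier estimates in survival analysis, we will use the Log-Rank test" and/or Cox models. It gives no censoring rule and no rule for competing events.
- **Safety Outcomes:** death is a serious adverse event, but death attributed to COVID-19 is not.

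**The concern.** Three consequences follow from ending efficacy follow-up at discharge.

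1. **Conflict.** A patient who goes home before day 30 has left efficacy follow-up, but an efficacy outcome at 30 days is still due. Serious adverse event reporting would not fill the gap, because deaths attributed to COVID-19 are outside it.
2. **Informative censoring.** With no respiratory data after discharge and no stated rule, the default is to censor at discharge. Kaplan-Meier then treats discharged patients as if they had the same future risk as those still in hospital. They were sent home because they were better. Death before respiratory failure raises a similar problem and also has no rule.
3. **Primary outcome.** Anyone still in hospital after day 14 is already an event. The composite therefore amounts to not leaving hospital alive and never ventilated by day 14. Whatever happens after such a discharge is not counted, and in an open-label trial the discharge decision is made with the allocation known.

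At stake are a readable risk curve for a clinically important secondary outcome, a consistent basis for 30-day mortality, and knowledge of whether early discharges were durable.

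**Working it through.** **Step 1. Can day 30 be reached with the contacts already planned?** If a patient is discharged d days after randomisation, safety reporting runs to day d + 30. Since d ≥ 0, this is at or beyond day 30 from randomisation for every discharged patient. The mortality line in Data collection and management also has no discharge limit. The data can therefore be obtained. The defect is that Follow-up says otherwise and that the origin of the 30 days is not stated.

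**Step 2. Effect of censoring at discharge.** The documents give no failure or discharge rates, so these inputs are assumptions: daily respiratory failure f = 3% in both arms; daily discharge g = 10% in one arm and 7% in the other; constant rates; no failure after discharge; no deaths.

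Actual incidence by day 30 = f/(f + g) × [1 − (1 − f − g)^30].

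- g = 10%: 0.03/0.13 × (1 − 0.87^30) = 0.2308 × (1 − 0.0153) = 0.227.
- g = 7%: 0.03/0.10 × (1 − 0.90^30) = 0.300 × (1 − 0.0424) = 0.287.

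Kaplan-Meier with discharge as censoring sees only the 3% daily risk among those still in hospital: 1 − 0.97^30 = 1 − 0.401 = 0.599 in both arms.

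| Daily discharge (assumed) | Actual 30-day incidence | One minus Kaplan-Meier |
|---|---|---|
| 10% | 23% | 60% |
| 7% | 29% | 60% |

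**Step 3. Other assumptions.** Let p be the share who fail before discharge under constant hazards, and h the discharge hazard. The failure hazard is a = h·p/(1 − p). With p = 20% and h = 1/8 per day, a = 0.125 × 0.20/0.80 = 0.03125. Actual day-30 incidence is 0.20 × [1 − exp(−0.15625 × 30)] = 0.198. One minus Kaplan-Meier is 1 − exp(−0.03125 × 30) = 0.608. For p from 10% to 30% and h from 1/5 to 1/10 per day, actual incidence is about 10% to 30% and one minus Kaplan-Meier about 28% to 92%. The direction is the same throughout; the size depends on the assumptions.

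**Step 4. Primary composite.** The Sample Size section expects 54.8% versus 20% events with 29 per group. The usual two-sided formula without continuity correction gives 30 per group for those rates, and 29 with the control rate rounded to 55%. Power at 29 is 79.8%. The stated size is reproduced closely enough, and this point does not alter it.

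Suppose a share r of apparent successes have an event after discharge, equal in both arms (an assumption). Expected reclassified patients are 29 × 0.452 × r (deferred) and 29 × 0.80 × r (early).

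| r (assumed) | Deferred | Early | Rates if counted | Power at 29 per group |
|---|---|---|---|---|
| 2% | 0.3 | 0.5 | 55.7% vs 21.6% | 77.5% |
| 5% | 0.7 | 1.2 | 57.1% vs 24.0% | 73.9% |
| 10% | 1.3 | 2.3 | 59.3% vs 28.0% | 68.0% |

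**The case against.** **Thirty-day mortality.** A reader might infer from Follow-up that it cannot be observed. The documents do not support that: collection at 30 days is scheduled, and safety contact reaches beyond it. Only the conflict between sections and the missing time origin stand.

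**The composite.** It is openly an in-hospital measure ("mechanical ventilation and/or hospitalization longer than 14 days and/or in hospital-death"), and replacing it would be partly a design preference. That stands. A reader might also infer that every relapse after discharge counts as success. That is too broad: patients ventilated during the stay, or kept longer than 14 days, are events whatever happens later.

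**Fragility.** A reader might infer that one missed event would reverse the result. That holds only for counts chosen at the threshold. With 29 per arm, 8 versus 16 gives p = 0.033 by uncorrected chi-squared but 0.061 by Fisher's exact test. Near the planned rates, 6 versus 16 gives p = 0.007 and 7 versus 16 gives p = 0.016 by uncorrected chi-squared, so one more early-arm event changes nothing.

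**Kaplan-Meier.** No rule for censoring at discharge is written; it is the default implied by the follow-up limit. In the illustration both arms have the same daily failure risk, so a hazard ratio of 1 correctly describes the rate among patients still in hospital. A reader might infer that censoring can create a difference. The example does not show that: the 23% versus 29% gap comes entirely from discharge speed, and censoring hides it. What stands is that the Kaplan-Meier curve cannot be read as the proportion of patients who develop respiratory failure.

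**Home data.** Blood gases are not measured at home, so treating discharged patients as event-free is itself an assumption. That is fair and should be stated in the plan.

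**Conclusion.** The concern holds in three limited parts.

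- **Inconsistency:** Follow-up conflicts with Secondary Outcomes and Data collection and management on 30-day mortality, and the time origin is missing.
- **Time to respiratory failure:** as planned, censoring would in practice fall at discharge and be informative, so Kaplan-Meier overstates cumulative risk. Under the assumed daily rates, 60% is reported in both arms against 23% and 29%. Those figures rest on constant rates, no failure after discharge and no deaths. Death without respiratory failure has no rule.
- **Primary composite:** a patient discharged alive and unventilated by day 14 who later is readmitted, ventilated or dies is scored a success. The number of such patients cannot be determined from the documents, and the 2% to 10% range above is illustrative only. This calls for a sensitivity analysis; it does not show that the primary comparison is invalid.

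**What to change.** 1. **Follow-up:** amend so that vital status, readmission and ventilation are ascertained for every randomised patient to day 30 from randomisation, through the existing post-discharge safety contact. State the same origin for the 30-day mortality outcome, so that it agrees with Secondary Outcomes and Data collection and management.
2. **Statistical Analysis Plan:** analyse time to respiratory failure to day 30. Keep patients discharged without failure in the risk set as event-free to day 30, stating the assumption that no unrecorded failure occurs at home. Treat death before failure as a competing event (cumulative incidence with Gray's test) or include it in the event, and say which.
3. **Primary outcome:** keep the composite. Add a sensitivity analysis that counts ventilation or all-cause death by day 30 wherever it occurs and adds readmission days to the hospital stay.

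The cost is a short amendment, a few lines in the analysis plan and a few added questions at a contact that is already planned. The downside is small: a few post-discharge events unrelated to plasma may be counted.

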**Safety Outcomes**

Adverse events (AE) will be defined as any unfavourable symptom, sign or test abnormality that is temporarily compatible with plasma transfusion. That includes COVID-19 symptoms that were not present at admission, complication associated to protocol issues (phlebitis, extravasation, etc.) and chronic disease worsening. Serious adverse event (SAE) will be defined as death, life-threatening adverse event, prolongation of hospitalization due to an adverse even, and any adverse event that requires an intervention. Death attributed to COVID-19 infection was not considered an SAE.

Any adverse event will be characterized by seriousness, duration, causality suspicion and intervention requirement. To establish causality the temporal relationship, previous pattern of transfusion-related AEs and exclusion of other causes will be reviewed.

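### Safety observation ends 30 days after discharge, so its length varies with hospital stay, and no fixed window or person-time rate makes the arms comparable

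*Combined protocol and SAP*

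**What the plan says.** The Follow-up section sets two end points. For efficacy, "The follow-up for efficacy outcomes will conclude at hospital discharge". For safety, "Safety outcomes will be reported until 30 days after hospital discharge". No safety day is fixed from enrolment or from transfusion.

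Hospital stay is also an outcome. The primary outcome is "Composite outcome of mechanical ventilation and/or hospitalization longer than 14 days and/or in hospital-death", and the secondary outcomes include "length of hospitalization; 30 day-mortality".

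The Safety Outcomes section defines an adverse event as "any unfavourable symptom, sign or test abnormality that is temporarily compatible with plasma transfusion" (the third-last adverb-like term is presumably meant as temporally). It then widens the scope: "That includes COVID-19 symptoms that were not present at admission, complication associated to protocol issues (phlebitis, extravasation, etc.) and chronic disease worsening". It also says "Death attributed to COVID-19 infection was not considered an SAE", while Data collection and management records all-cause mortality at discharge and at 30 days.

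Under Intervention and comparison, the early arm receives plasma on the day of enrolment. The deferred arm receives it only if PaO2/FiO2 falls below 200 or if the patient is still in hospital with symptomatic disease more than 7 days after enrolment.

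The Statistical Analysis Plan contains no analysis of adverse events: no test, no window, no person-time rate and no adjustment for exposure.

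**The concern.** Safety is the second specific objective. Its observation time is stay plus 30 days, and stay is something early plasma is intended to change. If mean stay differs between arms, so does the time in which an event can be counted. Events that accrue with time, such as worsening chronic disease or new COVID-19 symptoms, would then be commoner in the longer-stay arm even at the same daily rate. A table of counts or percentages by arm would mix harm with length of observation, and nothing in the plan would let a reader separate the two.

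**Working it through.** **Inputs.** From the documents: the window ends at discharge plus 30 days (Follow-up), and there are 29 patients per group (Sample Size). The documents give no stay by arm and no adverse event rate, so both are assumed below and shown as ranges.

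**The plan's own figure.** There is no stated safety figure to reproduce. The 29 per group is used only as an input. For 54.8% versus 20%, two-sided 5% and 80% power, the pooled normal formula gives 30 per group, or 29 if the second rate is 19.8% (the rounded 35-point reduction). The sample size is not affected by this point.

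**Step 1: observation time.** Window W = L + 30, where L is days from enrolment to discharge. At an equal constant daily rate r, expected events are r × W, so the count ratio is (L_long + 30) / (L_short + 30).

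| Assumed stays (days) | Windows (days) | Count ratio |
|---|---|---|
| 8 vs 10 | 38 vs 40 | 1.05 |
| 8 vs 12 | 38 vs 42 | 1.11 |
| 7 vs 14 | 37 vs 44 | 1.19 |
| 10 vs 20 | 40 vs 50 | 1.25 |

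Over a window fixed from enrolment the ratio is 1.00.

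**Step 2: proportion with at least one event.** P = 1 − exp(−r × W). For 7 vs 14 days at r = 0.01: 1 − exp(−0.37) = 30.9% and 1 − exp(−0.44) = 35.6%, a difference of 4.7 points. For r from 0.005 to 0.02 the difference is:

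- 0.8 to 1.8 points for 8 vs 10 days
- 2.9 to 6.2 points for 7 vs 14 days
- 4.0 to 8.1 points for 10 vs 20 days

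**Step 3: chance of a spurious significant excess.** With 29 per arm, if a two-sided 5% test were run, the approximate chance of a significant excess in the longer-stay arm is 3.0% to 3.4% (8 vs 10), 4.7% to 6.9% (7 vs 14) and 5.7% to 9.1% (10 vs 20). The nominal figure in that direction is 2.5%.

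**Step 4: the transfusion-linked definition.** Suppose only time after transfusion can yield a countable event, and a deferred patient is transfused on day 8, an illustrative day just past the 7-day criterion. The countable time is then L + 30 − 8.

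- Early 8 days, deferred 12 days: 38 vs 34, ratio 34/38 = 0.89
- Early 7 days, deferred 14 days: 37 vs 36, ratio 36/37 = 0.97
- Early 10 days, deferred 20 days: 40 vs 42, ratio 42/40 = 1.05

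Deferred patients who are never transfused lower these ratios further. The direction can therefore go either way.

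**Step 5: what a fixed window cannot do.** Suppose events are recorded at 0.04 per day in hospital and 0.01 per day afterwards (assumed), with stays of 7 vs 14 days.

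- Current window: 0.04×7 + 0.01×30 = 0.58 vs 0.04×14 + 0.01×30 = 0.86, ratio 1.48
- Days 0–30: 0.04×7 + 0.01×23 = 0.51 vs 0.04×14 + 0.01×16 = 0.72, ratio 1.41

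Most of that imbalance comes from time in hospital, not from the discharge-based end point.

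**Step 6: feasibility.** Discharge cannot precede enrolment, so discharge plus 30 days is never before day 30. Every survivor who completes follow-up is already covered for days 0–30.

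**The case against.** The strongest case against has four parts.

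- **Transfusion-linked definition.** Many late events may not qualify as adverse events, and an untransfused deferred patient may have few that do. This stands as a limit on direction. A reader might infer that the longer-stay arm is bound to show more events; Step 4 shows that the documents do not support that. It does not remove the problem, because the definition sets no time limit and expressly takes in background disease events.
- **No comparison is planned.** The safety objective is not worded as a comparison and no between-arm test is specified. That is correct, but in a randomised trial adverse event counts set out by arm will be read as a comparison.
- **No expected stay is given.** A reader might infer different stays from the 54.8% and 20% in the Sample Size section. Those rates are for the whole composite of ventilation, long stay or death, and in-hospital deaths shorten observation. They do not show that the windows will differ, or by how much.
- **Detection in hospital.** A reader might infer a much larger distortion from the ratio of in-hospital days alone, since the daily records run only to discharge or day 30 (for example "Hemodynamics daily until day 30 or discharge"). But that section lists no adverse event collection either before or after discharge, so it does not show where events are detected. Step 5 also shows that such an effect would not arise from the discharge-based end point and would largely survive its correction.

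The current rule also has a merit: every survivor transfused in hospital is followed for at least 30 days after plasma. A days 0–30 comparison gives a deferred patient transfused on day 8 only 30 − 8 = 22 such days. That cost is real, but later events would still be reported.

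**Conclusion.** The point holds in a limited form. Safety observation time depends on a post-randomisation outcome, and the plan offers neither a fixed window nor a person-time rate, so adverse event counts by arm are not strictly comparable. At equal constant rates the longer-stay arm is expected to show about 5% to 25% more events. That range rests entirely on the assumed stays. The net direction in this trial is uncertain because of the transfusion-linked definition and the conditional plasma in the deferred arm. Death is less affected, since all-cause mortality is recorded separately. This is a cheap improvement to the plan, not evidence that its safety findings would favour either arm.

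**What to change.** In Follow-up and in the Statistical Analysis Plan, state that the between-arm adverse event summary covers days 0 to 30 from enrolment in both arms, and counts events regardless of transfusion status. Report overall rates per person-day of observation alongside it, with observation ending at death where that comes first. Keep reporting all events up to 30 days after discharge, descriptively and by time since transfusion. Do not compare arms separately for in-hospital and post-discharge time, because that split conditions on the same post-randomisation variable.

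The cost is a few sentences and a change to the safety tables, with no new visits. The adverse event definition needs a matching line so that events in untransfused deferred patients are recorded on the same terms.

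Two downsides should be stated in the plan. Deferred patients transfused late have fewer than 30 post-transfusion days inside the compared window. And a common window does not remove differences caused by closer observation in hospital.
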